**Fig. 2 Fig2:**
[figure not shown]
CONSORT flow diagram [36] showing subject allocation to the intervention conditions

The study’s assessment and session timings are as follows: The baseline assessment session is delivered at enrollment, serving as the initial evaluation point. Between the baseline and the first session, approximately 1 to 2 weeks elapse. Subsequent sessions are held weekly thereafter. The mid-intervention assessment occurs after the second session but before the third, either on the day of the third session or 1 day prior. Similarly, the final assessment takes place after the fifth session, either on the same day or 1 day after. Additionally, a follow-up assessment is conducted 3 months after the conclusion of the intervention. In-person sessions are held at one of the NGO collaborators’ offices, providing a conducive environment for participant engagement and support.

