#### Sample size

An a priori power analysis based on a medium effect size estimation [37, 38] indicated that a total of 45 participants are needed (planned main statistical test is ANOVA repeated measures, within-between interaction; *f* = 0.25; statistical power = 0.95; *α* error probability = 0.05; three groups, four main measurements (pre-intervention, mid-intervention, post-intervention, and follow-up). Power analysis was computed using the G*Power 3.1 program [39].

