The improvement in the mental health and well-being scores within and between the groups will be examined using mixed-effects linear regression with a random intercept and slope over time (three assessments: baseline, after session 2, and post-treatment) and fixed effects for treatment assignment. The 3-month follow-up data will be analyzed using linear mixed effects model that incorporates random intercepts for participants and facilitators. Additionally, we may consider including random slopes for time if the data structure warrants it. If ICC analyses will indicate the presence of a hierarchical structure, we will proceed with conducting multilevel analyses. In addition, we will incorporate fixed effects for time and intervention condition and include any necessary covariates. We intend to perform longitudinal analyses in order to ascertain the long-term effects of the intervention. To evaluate changes in outcome measures from the initial measurement to each subsequent assessment, we plan to employ repeated measures ANOVA, where the data is complete, or mixed effects models, where data is incomplete. Moreover, we acknowledge that the linear mixed-effects model allows for the inclusion of covariates (we plan to control for demographics), and this flexibility makes it a robust alternative to repeated measures ANOVA, especially in complex datasets. The use of covariates was taken into account appropriately in the mixed-effects model, which is another reason we plan this approach when dealing with missing or incomplete data. The results of the other measures—demographic variables and therapeutic alliance as potential moderators and mediators—will be examined in an exploratory manner, utilizing regression models or mediation analyses. The error probability and the issue of multiple testing will be addressed either by employing the Bonferroni correction or the false discovery rate correction. Missing data—over 5%—will be handled with multiple imputation methods. Oversight and monitoring of the data collection process is conducted by the principal investigator and the project manager. Check-in regular meetings are held to review the progress of data collection, address any issues that may arise, and ensure compliance with the study protocol and ethical guidelines.

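### The 3-month model defaults to random intercepts with an optional slope, and the repeated-measures ANOVA assumes sphericity; if correlation falls over the 13-week gap, the error of the 3-month change is understated

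*Protocol article*

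**What the plan says.** The section on data collection, management and analysis describes three analyses.

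- **Baseline, mid and post:** "mixed-effects linear regression with a random intercept and slope over time (three assessments: baseline, after session 2, and post-treatment". The slope is firm.
- **3-month follow-up:** "The 3-month follow-up data will be analyzed using linear mixed effects model that incorporates random intercepts for participants and facilitators". The next sentence adds: "Additionally, we may consider including random slopes for time if the data structure warrants it". No criterion is given, and the text does not say whether this model uses all four visits or only baseline and follow-up.
- **Changes from baseline to each later assessment:** "we plan to employ repeated measures ANOVA, where the data is complete, or mixed effects models, where data is incomplete".

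The Sample size section adds "planned main statistical test is ANOVA repeated measures, within-between interaction", with three groups and four measurements, the last being the follow-up.

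The Participant timeline section fixes the spacing. "Between the baseline and the first session, approximately 1 to 2 weeks elapse"; sessions are then weekly, the mid assessment falls at about session 3 and the final one at about session 5, and "a follow-up assessment is conducted 3 months after the conclusion of the intervention". The Primary outcomes section defines the primary outcomes as change from baseline to post-intervention, so the 3-month comparison is not primary.

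**The concern.** A participant random intercept with independent residuals gives every pair of visits the same correlation. Adding a facilitator intercept does not change that within-person pattern. Repeated-measures ANOVA with one pooled within-person error makes the closely related sphericity assumption. Two scores 18 weeks apart will often be less alike than two scores 2 weeks apart. If so, an error term averaged over all visit pairs is too small for the longest change and too large for the short ones.

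The plan is firm about the slope over a span of 5 to 6 weeks and leaves it discretionary once a 13-week gap is added, which is where the equal-correlation assumption is most doubtful. With about 15 people per arm, a look at the data for a random slope has little power, so the restrictive default is likely to stand. At stake is a claim of lasting benefit that is more likely to be false than the nominal 5% suggests. If the pooled ANOVA is used for the primary change as well, some precision is lost there.

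**Working it through.** **1. The plan's own figure.** Sample size: f = 0.25, α = 0.05, power 0.95, k = 3 groups, m = 4 visits. Within-person correlation ρ and nonsphericity ε are not stated; I take ρ = 0.5 and ε = 1. Then λ = N f² m ε/(1−ρ), df1 = (k−1)(m−1)ε and df2 = (N−k)(m−1)ε. At N = 45, λ = 45 × 0.0625 × 4/0.5 = 22.5, with 6 and 126 degrees of freedom, and power is 0.956. The minimum is 44, and 45 gives three equal groups, so the stated total is reproduced with sphericity assumed. For scale, power at N = 45 is 0.88 if ε = 0.7 and 0.84 if ε = 0.6.

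**2. Visit times.** Session 1 is at week 1-2. Session 3 (mid) is two weeks later, week 3-4. Session 5 (post) is at week 5-6. Follow-up is about 13 weeks after that. Midpoints: weeks 0, 3.5, 5.5 and 18.5, so the gaps are about 3.5, 2 and 13 weeks.

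**3. Formula.** With equal variances, the variance of a change between visits j and k is 2σ²(1−r_jk). A pooled or compound-symmetry error replaces r_jk by the mean r̄ of the six pairwise correlations. So the model SE divided by the true SE is √[(1−r̄)/(1−r_jk)].

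**4. Assumed correlations.** The article gives none. Patterns A to C use r = b·exp(−φ·lag in weeks).

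| Pattern (b, φ) | r baseline-post | r baseline-3 months | r̄ | SE ratio, 3 months | SE ratio, post |
|---|---|---|---|---|---|
| A (0.75, 0.02) | 0.672 | 0.518 | 0.624 | 0.883 | 1.07 |
| B (0.80, 0.04) | 0.642 | 0.382 | 0.562 | 0.842 | 1.11 |
| C (0.90, 0.06) | 0.647 | 0.297 | 0.542 | 0.807 | 1.14 |

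Worked for B: the six correlations are 0.695, 0.642, 0.382, 0.738, 0.439 and 0.476, sum 3.372, mean 0.562. At 3 months √(0.438/0.618) = 0.842; at post √(0.438/0.358) = 1.106.

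Milder patterns add a stable person effect (0.5, 0.4 or 0.3 of the variance) to a decaying part (0.2, 0.3 or 0.4; correlation 0.7 per 3 weeks) and measurement error (0.3). They give 3-month ratios of 0.935, 0.917 and 0.904, and post ratios of 1.027, 1.036 and 1.044. Harsher patterns, pure exponential decay with no measurement error, give 3-month ratios of 0.735 to 0.847.

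**5. Test size.** Null simulation, 45/3 = 15 per arm, complete data, 20,000 trials, Metaverse versus Waitlist, two-sided 5%:

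| | A | B | C |
|---|---|---|---|
| 3-month change, pooled error | 8.4% | 9.8% | 11.6% |
| Baseline-to-post change, pooled error | 3.4% | 3.2% | 2.6% |

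With visit-specific error the 3-month test rejects 4.9% to 5.0%. Under the milder patterns, pooled 95% intervals for the 3-month change cover 92% to 93%, a test size of about 7% to 8%.

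**6. When the problem disappears.**

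- Equal correlation of 0.5: ratio 1.00, test size 4.9%.
- Baseline and follow-up only: ratio 1.00, coverage 95%.
- Random slope added (checked for the milder and the pure-decay patterns): ratio 1.02 to 1.04, coverage 95% to 96%.
- Arm difference in the 3-month score itself, rather than in change, with equal variances: ratio 1.00.

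**The case against.** The strongest reply is that the plan does not commit to the restrictive model. It permits a slope, and falling correlation is the very situation in which the data would warrant one. It does not say that all four visits enter the follow-up model. The ANOVA for changes from baseline to each later assessment can be read as a series of two-visit comparisons, where sphericity holds trivially. No correlations are given, so any size is assumed. The four-visit interaction test itself stays between about 5% and 7% under patterns A to C. Covariance structure and sphericity corrections commonly sit in the statistical analysis plan, which is not shown.

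Most of this stands, and it rules out three stronger readings. A reader might infer that the 3-month model has random intercepts only; the slope sentence contradicts that. A reader might infer that the 3-month confidence intervals are too narrow as a matter of fact; that needs falling correlation, all four visits, no slope and a change-from-baseline contrast, and the article settles none of these for certain. A reader might infer that the primary analysis is damaged; the three-visit model has a firm slope and is not affected, so the baseline-to-post loss arises only under a pooled four-visit analysis.

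What the reply does not remove is the choice written on the page. The point is not that a covariance structure goes unnamed. The article names a restrictive default for the longest interval, a richer one for the short interval, and a switch without a criterion between them. It also names a four-measurement ANOVA as the main test, and that route has no slope option.

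**Conclusion.** The concern holds in conditional form. If correlation declines with time, all four visits are analysed together and the slope is not added, the standard error of the baseline-to-3-month change is about 10% to 20% too small (7% to 19% across patterns A to C and the milder ones), and the nominal 5% test rejects about 7% to 11% of the time. Pure decay without measurement error would be worse. Under the pooled ANOVA the baseline-to-post standard error is about 3% to 14% too large, 7% to 14% under patterns A to C. All correlations are assumptions; the direction follows from the spacing once correlation declines. This bears mainly on the claim of long-term effect. It is worth correcting before analysis but does not undermine the trial.

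**What to change.** Do not leave the follow-up covariance to a data-driven choice. For each outcome, fit one model to all four visits with visit as a category, arm-by-visit terms and an unstructured within-person covariance (4 variances and 6 covariances), with small-sample degrees of freedom such as Kenward-Roger. Read both the post-intervention and the 3-month contrasts from it. The least change that would serve is to make the random slope firm in the follow-up model. If the repeated-measures ANOVA is kept, apply the Greenhouse-Geisser correction to the interaction and use visit-specific error for the contrasts.

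The cost is a rewording of the analysis paragraph, a few more covariance parameters and fewer error degrees of freedom. With 45 complete participants, a visit-specific contrast has 45 − 3 = 42 degrees of freedom against 3 × 42 = 126 for the pooled error. The critical value rises from 1.979 to 2.018, or about 2%.

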The Intake aims to assess participants if they are eligible for the study and introduce them to the goals of the program. The baseline assessment is conducted before the first session. A step-by-step guide about accessing and completing the survey is provided. Clarification of any questions or concerns are addressed. Session 1 focuses on facilitating an open discussion on participants’ needs, challenges, and cultural adjustment issues. It aims to create a safe and inclusive environment where participants can share their thoughts, concerns, and experiences, setting the tone for the support program. Session 2 focuses on the overall well-being of Ukrainian refugees and introduces strategies to enhance it. Session 3 focuses on perceived social support aiming at shedding light on its significance in our lives and providing practical tools to strengthen and enhance social networks. Session 4 focuses on mental health, with the aim of deepening participants’ understanding of mental health, reducing stigma surrounding mental health issues, and equipping them with essential knowledge and skills for promoting mental well-being. Session 5 is dedicated to raising awareness about gender-based violence (GBV), its various forms, and its profound impact on individuals and communities. Each session typically consists of 6 to 8 participants. The same 6–8 participants will attend each group session for the specific arm to which they are allocated. Each group will interact with the same members consistently from the first session to the last. Each arm is expected to have a minimum of two groups, and the formation of groups begins once a minimum of six participants have enrolled.

These groups convene weekly. To ensure that participants who miss a session are kept up to date, a briefing is conducted at the beginning of each session. This briefing provides a summary of the previous session’s discussions and activities, allowing all participants to stay informed and engaged, even if they were unable to attend the previous session.

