#### Assignment to interventions

The participants are randomly assigned to one of the three conditions (Metaverse, In-Person, Waitlist) using a sequence generated by the software randomizer.org.

The process of random allocation is executed by the project manager employing a straightforward random sequence, assigning one of three distinct numbers to each participant—either 1, 2, or 3, based on the number of the experimental condition.

Participants are enrolled by the project manager and trained facilitators from partner NGOs, with eligibility confirmed through thorough screening assessments. The project manager independently assigns participants to intervention groups, and allocation concealment is maintained by storing allocation lists as password-protected documents, accessible only after baseline assessments, ensuring that both participants and recruiters remain blind to group assignments until the intervention begins.

The Metaverse and In-Person groups are facilitated by two different psychotherapists, trained in evidence-based psychotherapies and group interventions, and who have at least 1 year of experience working with refugees. Both psychotherapists follow the same protocol structure (described in the “Interventions” section) to deliver the intervention.

The principal investigator and the statisticians conducting the data analysis remain unaware of the experimental condition until the study concludes.

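### Support-group clustering is modelled only if an unspecified ICC check indicates it, and the 3-month facilitator intercept probably cannot be separated from arm

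*Protocol article*

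**What the plan says.** The Interventions section of the protocol article sets groups of 6 to 8, at least two per arm, with closed membership: "Each group will interact with the same members consistently from the first session to the last". The Waitlist section has those participants assessed on the same schedule, with sessions offered only afterwards. So the design is partially nested: two arms have groups and one does not.

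The analysis paragraph (Data collection, management, analysis) describes two models. The baseline-to-post model has a random intercept and slope over time and a fixed effect for treatment. It covers the window of the primary outcomes and states neither a group nor a facilitator term. The 3-month model "incorporates random intercepts for participants and facilitators". Anything further is conditional: "If ICC analyses will indicate the presence of a hierarchical structure, we will proceed with conducting multilevel analyses". The support group is not named as a level, and no statistic or threshold is given.

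On therapists, Assignment to interventions says: "The Metaverse and In-Person groups are facilitated by two different psychotherapists". The Sample size section "indicated that a total of 45 participants are needed" and has no allowance for clustering.

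**The concern.** People who spend five weekly sessions in the same small group, with the same leader, tend to have correlated outcomes. That structure comes from the design, so the data need not be asked whether it exists. If it is left out when the correlation is above zero, standard errors are too small and differences are declared too often. A check based on about four groups has little information with which to trigger the correction.

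The facilitator intercept raises a separate problem. If each active arm has its own psychotherapist, facilitator and arm vary together, and the model cannot tell one from the other. The Objectives section makes the comparison between the active conditions an aim and Trial design claims an equivalence framework, so this contrast matters.

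**Working it through.** **Inputs from the article.** Total 45; three arms, taken as equal, so 45/3 = 15 per arm; groups of 6 to 8, so 15 splits as 8 + 7, giving two groups per active arm and four in all; f = 0.25, power 0.95, alpha 0.05, four measurements.

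**Assumed.** The ICC is not given, so a range of 0.01 to 0.20 is used.

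**The plan's own figure.** The Sample size section names its test: "planned main statistical test is ANOVA repeated measures, within-between interaction". With the unstated inputs at usual program defaults (correlation 0.5, epsilon 1):
- noncentrality = f² × N × m/(1 − rho) = 0.0625 × 45 × 4/0.5 = 22.5
- df = (3 − 1)(4 − 1) = 6 and (45 − 3)(4 − 1) = 126
- power = 0.955 at N = 45, and 0.939 at N = 42

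So 45 reproduces, with participants treated as independent.

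**Design effect.** 1 + (7.5 − 1) × ICC gives 1.33, 1.65 and 2.30 at ICC 0.05, 0.10 and 0.20. The correct standard error is the square root of this: 1.15, 1.28 and 1.52 times the unclustered one.

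**Type I error.** Simulated trials with no true difference, 15 per arm, groups of 8 and 7, and a two-sample t test that ignores groups. The ICC test is an F test of groups within arm on 2 and 26 df at 5%. In the two-stage column, group-level inference (2 df) is used only after a significant ICC test.

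| ICC | Metaverse vs In-Person, groups ignored | Active vs waitlist, groups ignored | ICC test detects | ICC estimate zero or negative | Metaverse vs In-Person, two-stage |
|---|---|---|---|---|---|
| 0.01 | 5.7% | 5.4% | – | – | – |
| 0.02 | 6.5% | 5.8% | 7% | 57% | 6.2% |
| 0.05 | 8.9% | 7.0% | 11% | 50% | 8.0% |
| 0.10 | 13.2% | 9.0% | 18% | 41% | 11.0% |
| 0.20 | 21.2% | 13.3% | 32% | 29% | 15.1% |

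Always using group-level inference holds the error at about 5% throughout.

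**Facilitator and arm.** With an intercept and two arm indicators the fixed-effect matrix has rank 3. Adding one facilitator column per active arm leaves it at 3, so no information about facilitator variance remains once arm is fitted. If both therapists worked in both arms, the rank would be 4. For scale, if therapists account for 2–5% of outcome variance (assumed), the difference between two therapists has an SD of √(2 × 0.02) = 0.20 to √(2 × 0.05) = 0.32 outcome SD. The unclustered standard error of the contrast is √(2/15) = 0.37.

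**The case against.** The strongest objection is that the article names no test. If a positive ICC estimate is enough to trigger group-level inference, simulated error for Metaverse versus In-Person is about 4.7%, 5.8% and 6.8% at ICC 0.05, 0.10 and 0.20, close to nominal. This stands. The detection rates above belong to one possible reading, a 5% test. But the result also depends on group-level degrees of freedom, and the article fixes neither that nor the trigger. The readings give materially different error rates and the text does not choose between them.

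A reader might infer that the standard errors will certainly be too small. The documents do not support that: they give no ICC, and at 0.01 to 0.02 the harm is slight. The simulations also use a simple t test, not the planned longitudinal model, and set aside the Bonferroni or false-discovery correction. They count false differences, not false claims of equivalence, though intervals that are too narrow would feed into either.

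A reader might also infer that the facilitator term spoils the primary analysis, that it is certainly confounded with arm, or that it has no meaning for the waitlist. It is stated only for the 3-month model. One therapist per arm is the natural reading, but the sentence does not exclude both working in both arms. The article also uses the word facilitator for staff who take consent and help with questionnaires.

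A separate analysis plan may add detail. That would not remove the conditional rule, which this article states.

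**Conclusion.** The point holds as a fault in a stated rule. A hierarchy built into the design is modelled only on an undefined condition, and the model for the primary outcomes states no group term. If the group ICC is 0.05 to 0.20 and there are two groups per active arm, ignoring groups gives a type I error of about 9–21% for Metaverse versus In-Person and 7–13% against the waitlist, and a 5%-level check would miss the clustering in most trials (detection 11–32%). With an ICC near 0.01 to 0.02, little changes.

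In the 3-month model, facilitator cannot be separated from arm if each psychotherapist leads one arm. In that case Metaverse versus In-Person is a comparison of format plus therapist at every time point, and no analysis of these data can undo it.

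**What to change.** - Delete the ICC condition.
- In all outcome models, prespecify a support-group random effect in the two active arms only, with each waitlist participant as a singleton, and use small-sample degrees of freedom, whatever the estimated ICC.
- State whether each psychotherapist serves one arm. If so, drop the facilitator random intercept and say that the Metaverse versus In-Person estimate combines format and therapist.

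The work is model code and a few sentences. The loss of apparent precision is not small. With four groups the Metaverse versus In-Person contrast has about 2 df, so the critical t is 4.30 instead of 2.05. In a simulation with groups of 8 and ICC 0.05, the mean interval was 2.2 times wider, and power for a difference of 0.8 SD fell from 59% to 21%. That is the precision this design has for that contrast.

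Having therapists work across arms is not part of this fix. Trial status estimated the end of recruitment as April 2024, so rescheduling may no longer be possible, and a therapist fixed effect on four groups would leave about 1 df for group variance.
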